# Long-term *Staphylococcus aureus* decolonization in patients on home parenteral nutrition: study protocol for a randomized multicenter trial

**DOI:** 10.1186/s13063-018-2732-2

**Published:** 2018-06-28

**Keywords:** Home parenteral nutrition, *Staphylococcus aureus*, Carriage, Long-term, Decolonization

## Abstract

**Background:**

Patients with long-term intestinal failure are usually treated by means of home parenteral nutrition (HPN) where they administer their nutritional formulation intravenously via a central venous access device (mostly a catheter). This implies that such patients are exposed to a lifelong risk of developing *Staphylococcus aureus* bacteremia (SAB). SAB poses a threat to both catheter and patient survival and may lead to frequent hospitalization and a permanent loss of vascular access. In other clinical settings, *S. aureus* carriage eradication has been proven effective in the prevention of *S. aureus* infections. Unfortunately, there is a complete lack of evidence in HPN support on the most effective and safe *S. aureus* decolonization strategy in *S. aureus* carriers. We hypothesized that long-term *S. aureus* decolonization in HPN patients can only be effective if it is aimed at the whole body (nasal and extra-nasal) and is given chronically or repeatedly on indication. Besides this, we believe that *S. aureus* carriage among caregivers, who are in close contact with the patient, are of great importance in the *S. aureus* transmission routes.

**Methods/design:**

The CARRIER trial is a randomized, open-label, multicenter clinical trial in Dutch and Danish hospitals that treat patients on HPN. A total of 138 adult HPN patients carrying *S. aureus* will be randomly assigned to a search and destroy (SD) strategy, a quick and short, systemic antibiotic treatment, or a continuous suppression (CS) strategy, a repeated chronic topical antibiotic treatment. The primary outcome measure is the proportion of patients in whom *S. aureus* is totally eradicated during a 1-year period. Secondary outcomes are time to successful eradication, long-term antimicrobial resistance, adverse events, patient compliance, incidence of (*S. aureus*) infections, catheter removals, mortality rates, *S. aureus* transmission routes, quality of life, and health care costs.

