### Study intervention

Prior to the start of the trial, HPN patients have been screened for *S. aureus* carriage with swabs of the nose, throat, rectum, exit-site catheter, and body regions on indication (e.g. stoma, wound, skin lesion). Subsequently, enrolled patients will visit the regular outpatient clinic appointments every 6 months, in accordance with current guidelines [10].

After randomization, patients will be allocated to one of the following two treatment strategies:*Search and destroy (SD) strategy* focuses on the quick and short, systemic antibiotic eradication of *S. aureus* (Fig. 4)*.* Patients will receive treatment with mupirocin nasal ointment, a chlorhexidine oropharyngeal rinse and body wash, and two systemic antibiotics for one week, according to the Dutch MRSA guideline [10]. Hygienic measures consist of wearing clean clothing every day and frequent change of towels and bed clothes during treatment. Combination therapy is indicated because of improved effectiveness and a decreased chance of developing resistance. After one cycle of treatment, a set of body swabs (nose, throat, rectum, exit-site catheter, and body regions on indication (e.g. stoma, wound, skin lesion) will be taken weekly for 3 weeks to confirm total eradication. In case of persistent *S. aureus* carriage, patients will be treated again. Patients will not receive more than three treatment cycles per round. A successful treatment is defined as three consecutive negative sets of surveillance cultures obtained at least 48 h after completion of treatment and distributed over a period of at least 14 days. Treatment failure is defined when a patient is still a *S. aureus* carrier after three treatment cycles. Relapse of *S. aureus* carriage will be subsequently monitored at the standard new swab rounds, every 3 months. In case of relapse, patients will be treated again as well.*Continuous suppression (CS) strategy* focuses on the continuous, topical eradication o*f S. aureus* (Fig. 5)*.* Whether or not patients are carriers during the year, they will receive mupirocin nasal ointment, an oropharyngeal chlorhexidine rinse, and body wash for extra-nasal body regions every month for 5 days. The same hygienic measures as in the SD strategy group will be applied. Standard swabs of the nose, throat, rectum, exit-site catheter, and other body regions on indication will be taken every 3 months to monitor full body eradication.

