### Outcome measures

*Primary outcome*
Proportion of patients in whom *S. aureus* is totally eradicated during a 1-year time period.Total eradication is defined as 100% of all swabs (nose, throat, rectum, exit-site catheter, and body regions on indication) being negative for *S. aureus* per measured time point.
*Secondary outcomes*
Secondary outcomes are listed in Table 1.

**Table 1 Tab1:** Secondary outcome measures

Secondary outcome measure	Data collection instrument or method
Incidence of *S. aureus* infections	(S)AE forms every 3 months
Overall incidence of infections	(S)AE forms every 3 months
Mortality	Data from electronic patient file
Long-term antimicrobial resistance	Culture results every 6 months and NGS
Number of catheter removals	Data from electronic patient file
Time to first catheter-related infection	(S)AE forms every 3 months and data from electronic patient file
Successful *S. aureus* eradication per body site	Culture results
Relapse rate of *S. aureus* carriage	Culture results and NGS
Transmission routes	Caregivers culture results and NGS
*S. aureus* transmission routes	NGS
Adverse events	(S)AE forms every 3 months
Predictors for infections and treatment failure or success	Binominal regression analysis
Patient compliance	Medication files, counting pills, trial-specific medication diary, modified Morisky Medication adherence questionnaire
Generic health related quality of life	EuroQol 5 dimension, 5 levels questionnaire (EQ5D-5 L)
Treatment satisfaction	TSQM vII questionnaire
Healthcare related costs	iMCQ questionnaire

*iMCQ* iMTA Medical Consumption Questionnaire, *NGS* next-generation sequencing, *(S)AE* (serious) adverse event, *TSQM* Treatment Satisfaction Questionnaire for Medication

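### Time to successful eradication is a secondary outcome in the abstract but not in Table 1, and timing each arm on its own swabs would favour SD

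*Protocol article*

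**What the plan says.** The abstract (Methods/design) puts the outcome first in its list: "Secondary outcomes are time to successful eradication, long-term antimicrobial resistance, adverse events, patient compliance". The Outcome measures section refers the reader to Table 1 for the secondary outcomes. Time to eradication is not there; the only time-to-event row is "Time to first catheter-related infection", a different outcome.

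The Study intervention section gives the two swab schedules.

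- **SD:** treatment includes "two systemic antibiotics for one week, according to the Dutch MRSA guideline". Afterwards, swab sets "will be taken weekly for 3 weeks to confirm total eradication". Success of treatment is "three consecutive negative sets of surveillance cultures obtained at least 48 h after completion of treatment and distributed over a period of at least 14" (counted in days). Persistent carriage leads to retreatment, with a limit: "Patients will not receive more than three treatment cycles per round". Relapse is then looked for at the 3-monthly rounds.
- **CS:** topical treatment is repeated whatever the carriage status, including "body wash for extra-nasal body regions every month for 5 days". Swabs "will be taken every 3 months to monitor full body eradication".

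The Follow-up section places swabs at months 3, 6, 9 and 12 and adds no earlier swab for CS. The Outcome measures section defines total eradication for all patients: every swab negative at the time point measured. The Secondary study parameter(s) section compares parameters between the groups by t-test, Wilcoxon, chi-square or Fisher test, according to type and distribution, at a two-tailed 5% level without multiplicity correction.

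**The concern.** A time-to-event outcome can be dated only when someone looks. SD is looked at within about two weeks of starting, and CS not until three months. Two patients who clear on the same day, one per arm, get recorded times that differ because of the calendar and not the treatment.

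The direction matters. The article describes SD as the quick strategy, and the sponsor intends to carry the findings into guidelines. A significant difference in time to eradication would be read as confirming speed when part or all of it reflected swab timing. The mismatch between the abstract and Table 1 adds to the problem, because the reader cannot tell whether the outcome is still planned or how it would be scored.

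**Working it through.** **The plan's own figure.** No figure is given for time to eradication. The only related number is the sample size, which belongs to the primary endpoint. With 77% against 55%, two-sided 5% (assumed) and 80% power, the unpooled normal formula gives

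n per arm = (1.960 + 0.842)² × (0.77 × 0.23 + 0.55 × 0.45) / 0.22² = 7.849 × 0.4246 / 0.0484 = 68.86, so 69 per arm and 138 in total.

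This matches the article. Nothing below changes it.

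**Step 1: earliest recordable times if clearance comes with the first course.** Inputs are the Study intervention and Follow-up sections. Weekly SD sets are assumed to fall at days 14, 21 and 28, and month 3 is taken as day 91.

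| Event | Day |
|---|---|
| SD, first negative set (7 + 7) | 14 |
| SD, confirmed success, minimum under the definition (7 + 2 + 14) | 23 |
| SD, confirmed success with weekly sets (7 + 21) | 28 |
| CS, first possible negative set | 91 |

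- First negative against first negative: 91 − 14 = 77 days (11 weeks, 2.5 months).
- SD confirmed on weekly sets against CS first negative: 91 − 28 = 63 days (9 weeks, 2.1 months).
- SD confirmed at the minimum against CS first negative: 91 − 23 = 68 days (2.2 months).

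Three SD cycles of about four weeks each take about 12 weeks, that is to about day 84. Every success in the first SD round is thus recorded before any CS success can be.

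**Step 2: gradual clearance, identical in both arms.** The documents give no distribution of clearance times, so an exponential one with permanent clearance was assumed and its median varied. There were 69 patients per arm and 1000 simulated trials per row. SD success was dated at the end of the first clean four-week cycle (day 28, 56 or 84), otherwise at the next quarterly set. CS success was dated at the first negative quarterly set. The arms were compared by log-rank test at 5%.

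| Median true clearance | Median recorded, SD (days) | Median recorded, CS (days) | Gap (months) | Rejection, own schedules | Rejection, common grid |
|---|---|---|---|---|---|
| 1 week | 28.0 | 91.0 | 2.1 | 100% | 0% |
| 2 weeks | 41.6 | 91.0 | 1.6 | 100% | 0.3% |
| 4 weeks | 56.3 | 91.0 | 1.1 | 100% | 3.9% |
| 8 weeks | 83.1 | 91.1 | 0.3 | 87% | 5.8% |
| 13 weeks | 138.1 | 139.9 | 0.1 | 30% | 4.2% |

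There is no true difference in any row, so rejection should be at most about 5%. A rank test, one of the tests the article names, also rejected in about 100% of trials for medians of 1 to 4 weeks, against 0 to 6% on the common grid.

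**Reading the table.** The gap in medians falls to 83.1 against 91.1 (8 days) at 8 weeks and 138.1 against 139.9 (under 2 days) at 13 weeks. The false-positive rate falls more slowly, because SD patients who clear early are still dated before day 91. Scoring both arms only at months 3, 6, 9 and 12 removes the artefact throughout.

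**The case against.** The strongest reply is that the outcome may not be in the plan at all. Table 1 omits it, and no start point, definition or test is stated for it. An analysis plan that is not shown could use the common swab points, and such detail is often left there. This stands in part: the bias arises only if each arm is timed on its own swabs, and the document does not say that it will be. But the abstract and Table 1 disagree in the text at hand, the unequal schedule is fixed by the design, and the general clause on between-group tests would reach the outcome if it were kept. No analysis can create CS data before month 3; it can only bring SD to the same grid.

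A reader might infer four stronger things, which the documents do not support.

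- *The schedule alone makes SD look months faster, and any test would be strongly significant.* Only if clearance is early. The documents give no clearance times, and allowing three SD cycles shows that slower clearance is contemplated.
- *SD can be recorded clear at day 9, giving a gap of 82 days.* Day 9 is 7 days plus the 48-hour minimum. It is not a scheduled swab day; the sets are weekly.
- *The visits cannot measure eradication time in CS.* They can, at 3-month resolution.
- *Eradication has no definition in CS.* The rule of three negative sets belongs to the SD treatment sequence, but the per-time-point definition under Outcome measures covers both arms.

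**Conclusion.** The point holds in limited form. Two things are certain from the text: the abstract lists an outcome that Table 1 does not, and the schedules give SD swabs from about week 2 but CS none before month 3. It follows that comparing times recorded on each arm's own swabs favours SD when true clearance is the same.

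The size is about 63 to 77 days if patients clear with the first course, and about a week or less in the medians if median clearance takes 8 to 13 weeks. This rests on weekly SD sets at days 14, 21 and 28, month 3 at day 91 and, for gradual clearance, an assumed exponential distribution common to both arms. The primary endpoint and the sample size are not affected. The point should be settled before analysis, but it does not threaten the trial's main conclusion.

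**What to change.** Reconcile the abstract with Table 1 in one of two ways.

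1. Delete time to successful eradication from the abstract's list of secondary outcomes.
2. Keep it and add a row to Table 1: time to the first of the common swab sets (months 3, 6, 9, 12) at which all swabs are negative, using the total-eradication definition from Outcome measures in both arms. Analyse it as interval-censored or discrete-time data on that grid.

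Under either option, report SD's time to three negative weekly sets only as description within that arm, with no between-arm p value.

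The cost is wording only, with no added visit or swab and no change to treatment. The downside is that the between-arm comparison has a 3-month resolution and cannot show whether SD clears patients faster within the first quarter. The CS schedule could not have supported that comparison in any case.

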**Discussion:**

The CARRIER trial is designed to identify the most safe and effective long-term *S. aureus* carriage decolonization strategy in HPN patients. This will eventually lead to a better understanding of long-term *S. aureus* decolonization treatments in general. The results of this study will have a great impact on our daily clinical practice, which eventually may result in less *S. aureus-*related infections.

**Trial registration:**

ClinicalTrials.gov; NCT03173053. Registered on 1 June 2017.

**Electronic supplementary material:**

The online version of this article (10.1186/s13063-018-2732-2) contains supplementary material, which is available to authorized users.

## Background

### Intestinal failure and home parenteral nutrition

The number of patients with intestinal failure in the Netherlands has increased exponentially over the past decade, from approximately 100 to 400 patients (Fig. 1). These patients depend on life-long home parenteral (intravenous) nutrition (HPN). HPN is a complex and time-consuming treatment focused around training patients to use their venous catheter and infusion pump at home. With the use of such venous access come frequent life-threatening complications, such as catheter-related bloodstream infections (CRBSIs). The reported incidence of CRBSIs in expert centers ranges from 0.38 to 4.58 episodes per 1000 catheter days and accounts for approximately 70% of all HPN-related hospital admissions [1, 2]. These complications are a threat to both the catheter and patient survival and may lead to permanent loss of vascular access. Because most HPN patients are well-trained to perform complex aseptic techniques to manage their catheters, further improvement of these techniques will likely have no significant impact on infection prevention.

**Fig. 1 Fig1:**
[figure not shown]
Incidence of patients on home parenteral nutrition (HPN) from 1997 to 2017 in the Radboudumc Nijmegen, The Netherlands. The exponential increase of HPN patients is attributed to a higher patient survival, multimorbidity, and the increase of complex surgical procedures

### *Staphylococcus aureus* infections and carriage

*Staphylococcus aureus* related to catheter exit-site, tunnel infections, and bacteremia (SAB) may all lead to complicated infections resulting in catheter loss [1]. On top of this, SABs easily result in secondary metastatic infectious foci leading to high morbidity and mortality rates of 20 to 30% [3–5]. In addition to the psychological impact on patients, healthcare-associated costs are substantial; around $30.000 per infection [5].

By estimation, the prevalence of nasal *S. aureus* carriage in HPN patients is comparable to hemodialysis patients, over 30% [6]. Nasal *S. aureus* carriage is a well-defined risk factor for subsequent *S. aureus* infections, and vice versa. Finally, more than 80% of health care-associated *S. aureus* infections are endogenous of origin [7, 8]. Studies show that the risk of developing *S. aureus* infections is 11.5 times higher among colonized hemodialysis patients compared with uncolonized patients [9]. In addition, approximately 19% of dialysis patients who are *S. aureus* carriers develop a *S. aureus* infection each year [9]. Infection prevention is a key strategy to maintain venous access and to avoid hospitalization. As such, *S. aureus* carriage eradication is instrumental for infection prevention. Besides this, evidence is mounting that *extra-*nasal *S. aureus* colonization is more common than previously believed. The usual decolonization strategies with only mupirocin nasal ointment are probably insufficient because extra-nasal body regions remain colonized with *S. aureus*. Finally, the role of *S. aureus* transmission to the HPN patient by a close partner or caregiver is unclear. Of note, the setting of HPN support poses a unique additional challenge here, since the caregiver is a critical factor in *S. aureus* carriage and transmission because the management of the patient’s venous catheter is often performed by the partner on a continuous basis.

### Rationale for *S. aureus* decolonization in HPN patients

The above demonstrates that evidence-based recommendations for *S. aureus* decolonization are needed, specifically for HPN patients and their caregivers. Unfortunately, current guidelines do not provide such recommendations; patients are currently treated—mostly based on “expert opinion”—with oral antibiotics, topical antibiotics, or nothing at all. This results in large treatment variations between the hospitals and even between clinicians.

We hypothesized that long-term *S. aureus* decolonization in HPN patients can only be effective if the decolonization treatment is aimed at the whole body (nasal and extra-nasal) and is given chronically or repeatedly on indication. The aim of the CARRIER trial is to improve patient care by reliably identifying the most effective and safe long-term *S. aureus* carriage decolonization strategy in HPN patients. Ultimately this will lead to less antimicrobial resistance, less catheter removals, and lower mortality rates. The CARRIER trial protocol was written in accordance with the Standard Protocol Items: Recommendations for Interventional Trials (SPIRIT). The SPIRIT checklist has been included as Additional file 1.

## Methods

### Design

The CARRIER trial is a multicenter, randomized controlled, open label, superiority trial in adult HPN patients carrying *S. aureus.* It aims to investigate the most effective and safe long-term *S. aureus* carriage decolonization strategy. The trial will recruit 138 patients that will be randomized to either a “search and destroy” (SD) group or a “continuous suppression” (CS) group (Figs. 2 and 3). The study design mirrors the real-life setting with respect to costs and effects.

**Fig. 2 Fig2:**
[figure not shown]
Study design of the CARRIER trial. Seven hundred parenteral nutrition patients will be screened for *S. aureus* colonization. A total of 138 *S. aureus* carriers will be included, of which 69 patients will be randomized to the search and destroy group and 69 patients to the continuous suppression group

**Fig. 3 Fig3:**
[figure not shown]
Schedule of enrollment, interventions, and assessments. Schedule of enrollment, interventions, and assessments according to the SPIRIT 2013 guidelines. *NGS* next-generation sequencing, *EQ5D-5 L* EuroQol 5 Dimensions, 5 levels, *TSQM* treatment satisfaction questionnaire measurement, *iMCQ* iMTA Medical cost questionnaire, *M* month(s). *In case of *S. aureus* eradication failure

#### Setting

The setting of this study is the outpatient clinic of the Endocrinology and Metabolism department of one Dutch academic hospital and the Gastroenterology and Hepatology departments of one Dutch and two Danish academic hospitals. The expected duration of this study is 3 years (6 months of preparation time and 2.5 years for enrollment and follow-up). The Danish HPN population is very similar to the Dutch HPN population in terms of infection rates, methicillin-resistant *S. aureus* (MRSA) prevalence, provided healthcare, healthcare system, and (benign) diseases leading to intestinal failure.

#### Trial population

All adult patients with intestinal failure on HPN will be screened for *S. aureus* carriage. With the expectation that at least 30% of the HPN patients are *S. aureus* carriers, approximately 700 patients will need to be screened. In case *S. aureus* carriage is confirmed, the patient will be screened for further eligibility and asked to enroll in the trial.

#### Inclusion criteria

In order to be eligible to participate in this study, a patient must meet all of the following criteria:Patient is fully able to understand the nature of the proposed intervention.Patient is diagnosed with intestinal failure and receives HPN.Written informed consent is provided by the patient before entering the trial.Age ≥ 18 years.Estimated life expectancy ≥ 1 year.Patient colonized with *S. aureus* (nasal and/or extra-nasal).

#### Exclusion criteria

A patient who meets any of the following criteria will be excluded from participation:Cannot be expected to comply with the trial plan (substance abuse, mental condition).Pregnant or breastfeeding women.Continuous exposure to MRSA (e.g., pig farmer).Allergy for both chlorhexidine and/or betadine.No options for any of the study drugs (systemic and/or topical antibiotics) due to resistance, allergies and/or interacting co-medication.Active *S. aureus* infection.Currently on treatment with antibiotics active against *S. aureus*.Decolonization (including mupirocin) treatment in the previous 2 months.The presence of an irremovable nasal foreign body.Aspartate transaminase (AST) and alanine transaminase (ALT) levels more than five times the upper limit of normal or liver failure.

